# Table 1. Study Flow Chart

|  | Screening/Baseline period | Observation period | | | | | | | | | | | | | Follow-up period |
| --- | --- | --- | --- | --- | --- | --- | --- | --- | --- | --- | --- | --- | --- | --- | --- |
| Time of visit | V1 | V2 | V3 | V4 | V5 | V6 | V7 | V8 | V9 | V10 | V11 | V12 | V13 | V14 | V15 |
|  | B1  (1w pre-op) | D-3 | D0 | D1 | D2 | D3 | D7 | D14  ±2d | D28  ±5d | D60  ±5d | D90  ±5d | 180  ±30d | D270  ±30d | D365^8^  ±30d | 15 months ± 30 d after the end of observation period |
| Sign informed consent form | X |  |  |  |  |  |  |  |  |  |  |  |  |  |  |
| Demographic data | X |  |  |  |  |  |  |  |  |  |  |  |  |  |  |
| Medical and treatment history | X |  |  |  |  |  |  |  |  |  |  |  |  |  |  |
| Verification of inclusion/exclusion criteria | X |  |  |  |  |  |  |  |  |  |  |  |  |  |  |
| Physical examination | X |  |  | X |  |  |  |  | X |  | X |  |  | X | X |
| Serum pregnancy test^1^ | X |  |  |  |  |  |  |  |  |  |  |  |  |  |  |
| Start of prednisone administration |  | X |  |  |  |  |  |  |  |  |  |  |  |  |  |
| Surgical administration |  |  | X |  |  |  |  |  |  |  |  |  |  |  |  |
| End of prednisone administration |  |  |  |  |  |  | X |  |  |  |  |  |  |  |  |
| Vital signs ^2^ | X |  | X | X | X | X | X | X | X | X | X | X | X | X | X |
| ECG | X |  | X | X |  |  | X | X | X | X | X | X | X | X | X |
| Chest X-ray | X |  |  |  |  |  |  |  | X |  |  |  |  | X | X |
| Blood routine^3^ | X |  |  | X |  |  | X | X | X | X |  | X |  | X | X |
| Urine routine^3^ | X |  |  | X |  |  | X | X | X | X |  | X |  | X | X |
| Blood chemistry^3^ | X |  |  | X |  |  | X | X | X | X |  | X |  | X | X |
| Serum virology tests^3^ | X |  |  | X |  |  | X |  | X |  |  |  |  | X | X |
| Coagulation function test^3^ | X |  |  | X |  |  | X |  | X |  |  |  |  | X | X |
| Collection of lacrimal fluid | X |  | X | X | X | X | X |  |  |  |  |  |  | X | X |
| Collection of peripheral blood leukocytes | X |  | X | X |  |  | X |  |  |  |  |  |  | X | X |
| Collection of peripheral blood mononuclear cells^4^ | X |  |  |  |  |  |  | X | X |  |  |  |  | X | X |
| rAAV vector neutralizing antibodies in peripheral blood plasma^5^ | X |  |  |  |  |  |  | X | X |  | X |  |  | X | X |
| CYP4V2 protein antibodies in peripheral blood serum^5^ | X |  |  |  |  |  |  | X | X |  | X |  |  | X | X |
| General ophthalmological examination ^6^ | X |  |  | X | X | X |  | X | X | X | X | X | X | X | X |
| Best-corrected visual acuity^7^ | X |  |  | X | X | X |  | X | X | X | X | X | X | X | X |
| Color fundus photography | X |  |  | X | X | X |  | X | X | X | X | X | X | X | X |
| OCT | X |  |  | X | X | X |  | X | X | X | X | X | X | X | X |
| Color vision | X |  |  |  |  |  |  |  | X | X |  | X |  | X | X |
| Macular microperimetry | X |  |  |  |  |  |  |  | X | X |  | X |  | X | X |
| Contrast sensitivity | X |  |  |  |  |  |  |  | X | X |  | X |  | X | X |
| mfERG | X |  |  |  |  |  |  |  | X | X |  | X |  | X | X |
| MLMT | X |  |  |  |  |  |  |  | X | X |  | X |  | X | X |
| Adverse events |  | X | X | X | X | X | X | X | X | X | X | X | X | X | X |
| Concomitant medications, treatments |  | X | X | X | X | X | X | X | X | X | X | X | X | X | X |

Comments:

1. Blood pregnancy test should be performed within 1 week before administration.

2. Vital signs are measured at the following time points within 24 h after administration: Pre-dose (within 1 h) and 1 h ± 15 min and 3 h ± 30 min post-dose.

3. Laboratory tests (blood routine, urine routine, blood chemistry, Serum virology tests and coagulation function test) should be repeated if it is performed more than 1 week prior to administration.

4. PBMC immunoreactivity is detected by ELISpot method after isolation of PBMC cells from venous blood of patients.

5. Detection of rAAV vector neutralizing antibody and CYP4V2 protein antibody in peripheral blood: Collect venous blood from patients, separate plasma or serum and detect by ELISA. The subsequent detection is stopped if the detection is negative on two consecutive occasions.

6. General ophthalmological examination includes intraocular pressure, slit-lamp examination and ophthalmoscopy (direct ophthalmoscopy, indirect ophthalmoscopy, or preset lens).

7. Best-corrected visual acuity is measured using the ETDRS chart.

8. Patients should be followed up annually after the end of this study.

9. Test items judged as adverse reactions need to be repeated at subsequent visits until recovery or stabilization.

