| **Biological sample collection and testing:**  **Collection Points for rAAV Vector DNA Detection in Lacrimal Fluid:**  Tear is collected from subjects at pre-dose (baseline period), 3 h (D0), D1, D2, D3, D7, and D365 post-dose, and 15 months after the end of observation period to extract DNA. DNA samples are used to test the DNA concentration of rAAV vector and quantified using a validated real-time quantitative PCR (q-PCR).  **Collection Points for rAAV Vector DNA Detection in Peripheral Blood:**  Two mL of blood samples are collected from the upper limb vein of subjects and put into EDTA-anticoagulated blood collection tube (blood collection tube with purple cap) to separate leukocytes and extract DNA at each point at pre-dose (baseline period), 3 h (D0), D1, D7 and D365 post-dose, and 15 months after the end of observation period. DNA samples are used to test the DNA concentration of rAAV vector and quantified using a validated real-time quantitative PCR (q-PCR).  **Immunogenicity Blood Collection Points:**  Ten mL of blood samples are collected from the upper limb vein of subjects at each point at pre-dose (baseline period), D14, D28 and D365 post-dose, and 15 months after the end of observation period, and placed in BD 362761 peripheral blood mononuclear cell (PBMC) preparation tubes (CPT) to isolate PBMCs. PBMCs are used to test T cell immune response against rAAV vectors and T cell immune response against CYP4V2 protein, which are quantified using a validated ELISpot method.  Two mL of blood samples are collected from the upper limb vein of subjects and put into EDTA-anticoagulated blood collection tube (blood collection tube with purple cap) to obtain serum samples at each collection point at pre-dose (baseline period), D14, D28, D90 and D365 post-dose, and 15 months after the end of observation period. Plasma samples are used to detect rAAV vector neutralizing antibodies and quantified using a validated enzyme-linked immunosorbent assay (ELISA).  Two mL of blood samples are collected from the upper limb vein of subjects and put into blood collection tube containing coagulant (blood collection tube with orange-yellow cap) to obtain serum samples at each collection point at pre-dose (baseline period), D14, D28, D90 and D365 post-dose, and 15 months after the end of observation period Serum samples are used to detect humoral immune responses against CYP4V2 protein and quantified using a validated enzyme-linked immunosorbent assay (ELISA). |

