## 4.2 Exclusion Criteria

Subjects meeting any of the following criteria will not be eligible to participate in this study.

1) The patient lacks sufficient viable retinal photoreceptor cells, has less than 1 disc area of retina photoreceptor cells or has a retinal thickness of less than 100 μm.

2) Active choroidal neovascularisation (CNV) lesion secondary to BCD in the target eye judged by the investigator; or other ocular disorders that would preclude surgery or interfere with interpretation of the study endpoints;

3) Medications within 3 months prior to screening that may affect study observation (e.g., Lucentis, Avastin, aflibercept, conbercept, triamcinolone acetonide, steroids, etc);

4) The target eye has received the following intraocular surgical treatments (PDT, vitrectomy, cataract surgery and retinal laser therapy required during the clinical study, periocular vascular bypass surgery, etc.);

5) Currently taking or may require systemic medications that can cause ocular toxicity, such as Psoralen, Risedronate, or Tamoxifen;

6) Hypersensitivity to any component of the investigational drug, or allergic constitution (e.g., allergy to two or more drugs or food);

7) Abnormal findings of physical examination, vital signs, laboratory tests (hematology, urinalysis, blood biochemistry, coagulation function, immunological examination, female blood pregnancy test), 12-lead ECG, chest X-ray judged by the investigator as clinically significant;

8) Having any past or present medical history that may affect the safety of the study or the metabolic process of the drug, especially the medical history of cardiovascular, hepatic, renal, endocrine, gastrointestinal, pulmonary, neurological, hematological, oncologic, immunological or metabolic disorders and others that are thought clinically significant by the investigator;

9) Participation in any clinical study of drug or medical device within 3 months prior to screening;

10) Patients with rAAV neutralizing antibody titer greater than 1:1000 detected by immunogenicity test;

11) Females who are pregnant or lactating;

12) Subjects who are not suitable for participation in this clinical study due to other reasons judged by the investigator.

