### 9.3.3 Safety

The incidences of overall and various adverse events at this dose level are statistically analyzed, and descriptive statistical analysis is performed for safety measures such as laboratory tests, vital signs, ophthalmological examination, and ECG.

Descriptive statistical analysis for rAAV vector DNA concentrations in tear and peripheral blood leukocytes after a single dose at each dose level is performed.

Descriptive statistical analysis is performed for the positive rate of anti-drug antibody at this dose level.

Anti-CYP4V2 protein antibody concentration, rAAV2/8 virus neutralizing antibody concentration, cellular immune responses to rAAV2/8 capsid protein and CYP4V2 protein.

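### The rule that stops antibody testing after two consecutive negatives can end humoral follow-up at D14 or D28, and it does not match the unconditional schedule in the synopsis and section 6.1

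*Protocol*

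**What the plan says.** Table 1 of the protocol marks two antibody rows, rAAV neutralizing antibody in plasma and CYP4V2 antibody in serum, at V1 (baseline), D14, D28, D90, D365 and V15. Both rows carry footnote 5. The footnote is headed "Detection of rAAV vector neutralizing antibody and CYP4V2 protein antibody in peripheral blood" and ends: "The subsequent detection is stopped if the detection is negative on two consecutive occasions".

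The synopsis, under the immunogenicity collection points, lists these samples "at each collection point at pre-dose (baseline period), D14, D28, D90 and D365 post-dose, and 15 months after the end of observation period" and attaches no condition. The visit lists in sections 6.1.2 and 6.1.3 name both antibody tests at V8, V9, V11, V14 and V15, also without condition.

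Footnote 4 covers the cellular assay: "PBMC immunoreactivity is detected by ELISpot method after isolation of PBMC cells from venous blood of patients". It contains no stopping rule.

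Immunogenicity is one of the safety items in the synopsis and in section 7.1, which plans a curve of cellular and humoral immune data over time for each subject. Section 9.3.3 adds: "Descriptive statistical analysis is performed for the positive rate of anti-drug antibody at this dose level". It does not say whether that rate is cumulative or per visit, or how untested visits enter it.

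**The concern.** A stop after two negatives makes sense for a subject who was positive and has returned to negative. Footnote 5 applies it to everyone, including subjects who have not yet had time to respond. Two early negatives end the testing, with no earliest stopping date and no provision to restart.

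Whether a later antibody result exists then depends on the earlier antibody results, so the missing data are tied to the quantity being described. The earliest possible stop, at D14, comes about one week after the last prednisone dose on D7. The schedule, by contrast, runs to V15, which is 15 months past the one-year observation period, or about 27 months after dosing.

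The trial's primary objective is safety, and immunogenicity is among its safety measures. A statistical analysis plan can define the rate and its denominator, but it cannot supply results from tests that were never run.

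**Working it through.** The protocol states no immunogenicity rate, precision or power, so there is no figure to reproduce. The check applies the footnote to the schedule.

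**Inputs.** Table 1 and the synopsis give six antibody occasions: V1, D14, D28, D90, D365 and V15, of which 5 are post-dose. The rule is the last sentence of footnote 5, applied here to each antibody separately. The planned number of subjects is 3 + 9 = 12 (section 9.1.2).

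**Step 1: enumeration.** Take a subject who is negative at baseline, becomes positive at a given visit and stays positive.

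| First positive | Tested, baseline counted | Seen? | Tested, post-dose results only | Seen? |
|---|---|---|---|---|
| D14 | all six | yes | all six | yes |
| D28 | V1, D14 | no | all six | yes |
| D90 | V1, D14 | no | V1, D14, D28 | no |
| D365 | V1, D14 | no | V1, D14, D28 | no |
| V15 | V1, D14 | no | V1, D14, D28 | no |

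Tests lost with baseline counted: 5 − 1 = 4 of 5. Tests lost with post-dose results only: 5 − 2 = 3 of 5, and this needs D28 as well as D14 to be negative. Leaving baseline out of the count is therefore only a partial repair.

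**Step 2: direction of the distortion.** With all treated subjects in the denominator, the rule can remove positives from an ever-positive rate but cannot add any, so that rate falls or stays the same. A per-visit rate among those still tested behaves differently. Subjects with two negatives have left its denominator, so it is too high unless the stopped subjects later become positive as often as those still tested.

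**Step 3: illustration (assumed figures, not from the protocol).** Suppose all 12 subjects are baseline-negative, baseline counts, 6 convert by D365 and stay positive, and 2 to 4 of the 6 convert after D14.
- True ever-positive rate: 6/12 = 50%.
- Observed ever-positive rate: (6 − 2)/12 = 33% down to (6 − 4)/12 = 17%.
- D365 rate among those still tested: 4/4 or 2/2 = 100%, against a true 6/12 = 50%.

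A wider range, again by assumption: if 20% to 60% of converters are positive by D14 and a further 30% by D28, a true 50% reads as follows.
- Baseline counted: 0.5 × 0.2 = 10% to 0.5 × 0.6 = 30%.
- Post-dose results only: 0.5 × 0.5 = 25% to 0.5 × 0.9 = 45%.

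**Step 4: chance of missing anyone.** If a proportion s of subjects converts after testing has stopped, the chance of missing at least one of n is 1 − (1 − s)^n.

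| s (assumed) | n = 12 | n = 9 |
|---|---|---|
| 5% | 46% | 37% |
| 10% | 72% | 61% |
| 20% | 93% | 87% |

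Each missed converter among 12 changes the ever-positive rate by 1/12, about 8 percentage points.

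**Step 5: agreement between sections.** Under the footnote, a subject negative at V1 and D14 is not tested at V9, V11, V14 or V15. Under the synopsis and section 6.1, the same subject is tested at all four. Nothing in either place refers to the footnote.

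**The case against.** The strongest reply is that a footnote on a table row qualifies the schedule, and the visit lists merely repeat the schedule without it. On that view there is a missing cross-reference and no true contradiction. That is a fair reading, but it leaves the rule itself intact, and site staff working from section 6.1 alone would still act differently from staff working from Table 1. The footnote also stops detection, while the synopsis speaks of collecting blood, so samples might still be drawn. If they were stored, some results could be recovered, but the protocol does not say so.

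Several stronger readings are tempting and are not supported:

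- A reader might infer that the reported rate is biased low. Section 9.3.3 does not say which rate is meant, and a per-visit rate among those still tested would err upward.
- A reader might infer that late immune responses go unseen altogether. ELISpot testing against vector and CYP4V2 continues at D28, D365 and V15, a subject positive at baseline or D14 is not stopped at D14, and the comments to section 6.1.3 let the investigator add safety examinations. What can be lost is late antibody conversion after two early negatives.
- A reader might call immunogenicity a primary safety evaluation. The protocol lists it as one of six safety items, analyses it descriptively, and says in section 7.1 that ocular events are the focus.
- A reader might add that raw positivity includes antibody present before dosing, since the only bar to entry is "Patients with rAAV neutralizing antibody titer greater than 1:1000 detected by immunogenicity test". That is true, but a treatment-emergent definition can be left to the statistical analysis plan. Baseline samples and antibody concentrations are planned, so the data to apply one exist.

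**Conclusion.** The point stands in this form. Followed literally, footnote 5 can end antibody testing at D14, with 4 of 5 post-dose tests lost, if baseline counts. If it does not, testing can end at D28, with 3 of 5 lost. These counts follow from the document alone. In the subjects concerned, later antibody conversion is invisible, an ever-positive rate can only be understated, a per-visit rate among those still tested would be overstated, and the humoral part of the section 7.1 curves may consist of two or three points.

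The size of the distortion cannot be derived. The percentages above rest on assumed conversion rates and timing, on persistent positivity and, for the rate illustrations, on all subjects being negative at baseline. The footnote also needs reconciling with the synopsis and section 6.1, whichever way the sponsor decides. Because the fault lies in data collection, the protocol is the place to correct it.

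**What to change.** Delete the last sentence of footnote 5, so that both antibodies are tested at every scheduled visit through V15. Alternatively, limit it to subjects who became positive after dosing and then returned to negative on two consecutive tests. Whichever is chosen, give the same rule in Table 1, the synopsis and section 6.1.

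The cost is modest. Each subject who would have stopped at D14 needs at most 4 visits × 2 assays = 8 further determinations. For the 9 new subjects the upper limit is 9 × 8 = 72, all of them already in the unconditional schedule. At D28, D365 and V15 other blood is drawn anyway. At D90 the two 2 mL antibody tubes are the only scheduled blood sample, so a subject who would otherwise have been spared it has one small venepuncture.

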# 1. Study Background

## 1.1 Disease Background and Treatment Status

Bietti's crystalline dystrophy (BCD) is a special type of retinal degeneration with typical change of yellow-white flare crystalline deposits in the retina with atrophy of retinal pigment epithelium and choriocapillaris, which seriously jeopardizes visual acuity. Patients with BCD are rare in the West, with more patients in China and Japan, with a population prevalence of 1/24,000 ^[1]^, based on which it is estimated that there are 70,000 patients who are blind due to BCD in China. It is an important cause of blindness in working-age population ^[2]^ and currently there is no effective therapy.

BCD is inherited as an autosomal recessive trait and is caused by CYP4V2 mutations^[3]^. CYP4V2 gene is one of the proteins in the cytochrome P450 (CYP) superfamily, which is mainly distributed on the endoplasmic reticulum and mitochondrial inner membrane and is a terminal oxygenase involved in the synthesis and metabolism of a variety of endogenous and exogenous substances, as well as an omega-fatty acid hydroxylase that plays an important role in intracellular lipid metabolism ^[4, 5, 6]^. The mechanism of action is shown in Figure 1. CYP4V2 is a selective of omega-3 polyunsaturated medium-chain fatty acid hydroxylase and exhibits unique chain length selectivity with substrate specificity of myristate (C14) > lauric acid (C16) > palmitic acid (C12) ^[7]^; the endogenous substrate is omega-3 polyunsaturated fatty acids, mainly docosahexaenoic acid (DHA) and eicosapentaenoic acid (PA) in the eyes ^[8]^. CYP4V2 mRNA is widely expressed, mainly in retinal pigment epithelium (RPE) and photoreceptor cells in the eyes ^[8]^. Mutations in the CYP4V2 gene in patients with BCD lead to abnormal function of their encoded enzymes, which affects lipid metabolism and causes disease ^[6,7,8,9]^. RPE cells play an important role in the development and visual function of the eye and have important functions such as secreting growth factors, anti-oxidation, participating in visual circulation metabolism, maintaining the blood-retinal barrier, and phagocytosing outer segment membrane discs shed by photoreceptor cells ^[10]^. Lesions in RPE cells lead to retinal photoreceptor cell damage, resulting in retinal degeneration and other diseases.

[figure not shown]

Figure 1. CYP proteins are involved in lipid metabolism of omega-3 polyunsaturated medium-chain fatty acids ^[5]^

Currently, molecular genetic studies have identified multiple mutation sites in the CYP4V2 gene ^[11-15]^. As of August 2019, 86 pathogenic mutations of CYP4V2 gene are currently known, including 56 nonsense mutations, 12 splicing mutations, 11 deletions, 3 insertions, 2 deletions, and 1 large fragment deletion, see Table 2 (The Human Gene Mutation Database, http://www.hgmd.cf.ac.uk/ac/index.php). There is no effective treatment available for BCD worldwide.

Table 2. Summary of CYP4V2 gene mutation sites

| **Exon** | **Mutations** | **Effect** | **Allele frequency in 74 probands** |
| --- | --- | --- | --- |
| E1 | c.65T>A | p.L22H | 1 |
|  | c.214+1G>A | splicing site | 1 |
| E2 | c.215-2A>G | splicing site | 1 |
|  | c.219T>A | p.F73L | 5 |
|  | c.283G>A | p.G95R | 6 |
| E3 | c.335T>G | p.L112* | 2 |
| E4 | c.414-4_414del4bpinsA | splicing site | 1 |
|  | c.518T>G | p.L173W | 1 |
| E6 | c.681_4delTGAG | p.S227Rfs*1 | 1 |
| E7 | c.802-8_810del17bpinsGC | splicing site | 72 |
|  | c.802-8_810del17bpinsGT | splicing site | 5 |
|  | c.958C>T | p.R320* | 2 |
|  | c.965_7delAAG | p.321delE | 1 |
| E8 | c.992A>C | p.H331P | 15 |
|  | c.992A>G | p.H331P | 6 |
|  | c.994G>A | p.D332N | 1 |
|  | c.1062insA | p.V355Sfs*3 | 1 |
|  | c.1062-1063insA | p.V355Sfs*2 | 2 |
| E9 | c.1168C>T | p.R390C | 1 |
|  | c.1169G>A | p.R390H | 5 |
|  | c.1199G>A | p.R400H | 1 |
|  | c.1091-2A>G | splicing site | 15 |
| E10 | c.1126-6_1135del16bp | splicing site | 1 |
| E11 | c.1544T>G | p.I515S | 1 |

In recent years, significant progress has been made in gene therapy for inherited retinal degeneration. On December 20, 2017, FDA approved Luxturna, a RPE65 gene replacement therapy, for marketing. As the first gene replacement therapy drug for hereditary diseases in the history of the United States, Luxturna has opened a new era of gene therapy, brought new hope for the treatment of such diseases, and provided reference for the treatment of other single-gene hereditary diseases. Mutations result in loss of function of the protein encoded by target gene, and complementary DNA (cDNA) of the target gene is packaged into a vector and injected into the subretinal space, which has been found to partially improve visual function in patients in clinical studies ^[16-18]^. In terms of vector selection, recombinant adeno-associated virus vector (rAAV) has become the most commonly used and the most effective gene therapy vector in ophthalmology due to its advantages of good safety, low immunogenicity, ability to infect non-dividing phase cells, expression of exogenous genes for a long time in vivo, and specific tissue affinity for retinal photoreceptor cells. rAAV-mediated gene replacement therapy has demonstrated good safety and clinical effects in foreign clinical studies.

Mutations in the CYP4V2 gene result in loss of protein function and gene replacement therapy is theoretically safe and effective. In the previous study, our company successfully constructed CYP4V2 gene replacement therapy vector. The patient iPSC-RPE cells in vitro and CYP4V2 gene mutation mouse model were used to verify the efficacy and safety at cellular level of replacement therapy vector in mice, all of which achieved significant therapeutic effect without significant toxic and side effects. At present, intellectual property protection has been applied for this product. There are no clinical studies on replacement therapy for BCD worldwide, and the use of rAAV2/8-hCYP4V2 Ophthalmic Injection will fill this gap and bring good news to patients.

Preliminary study results are detailed in the Investigator's Brochure.

